**Abstract:**

Gastroparesis (GP), defined as delayed gastric emptying without any mechanical obstruction affects up to 10 million individuals in the United States. Improvement of symptoms is achieved in up to 50-60% of drug refractory patients treated with gastric electrical stimulation (GES), but this therapy has minimal or no effect on the acceleration of gastric emptying (GE). To address this therapeutic deficiency, we have added surgical pyloroplasty (PP) as a supplementary procedure to accelerate GE in drug refractory gastroparetics undergoing implantation of GES. Based on our experience, there was more than 70% improvement in total GP symptom scores (TSS) in the follow-up evaluation and GE was normalized in 60 % of GP patients who received combined GES and pyloroplasty, suggesting that the combination of PP and GES significantly accelerate gastric emptying and improve GP symptoms exceeding the results previously achieved by GES alone. Now, the question is whether pyloroplasty alone could be sufficient for the achievement of both subjective and objective goals of improvement in drug refractory gastroparesis. Therefore, in the current proposal, we plan to compare TSS outcome, quality of life and GE in drug refractory GP patients who will receive both GES implantation and PP during the surgery and then are evaluated during a GES-off or –On period based on a randomized double blind study design. As a secondary goal, we will also examine whether the baseline pyloric and antral interstitial cells of Cajal (ICC) counts as well as the presence of pyloric fibrosis could predict clinical response to PP.

42  
43  
44  
45 **Research Plan: A) Specific Aims**

46 **1)** To assess the effects of gastric electrical stimulation (GES) and pyloroplasty on total GP  
47 symptoms scores (TSS) and quality of life in drug refractory gastroparetic patients during GES -  
48 ON and GES -OFF periods.

49 **2)** To assess the effects of gastric electrical stimulation (GES) and pyloroplasty on gastric  
50 emptying of a radiolabeled marker in drug refractory gastroparetic patients during GES-ON and  
51 GES -OFF periods.

52 **3)** To understand whether pyloroplasty alone is effective for achieving both subjective and  
53 objective goals of improvement in drug refractory gastroparesis.

54 **4)** To understand whether the status of antral and pyloric ICC counts and/or the presence of  
55 pyloric fibrosis predicts the clinical outcome.

56  

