## C) Preliminary data

### C1) GES-ON plus Pyloroplasty:

A pilot study [abstract submitted to DDW 2016] was designed to assess the long term efficacy (follow-up visits: 3 to 38 months) and safety of combined GES implantation and PP in GP patients who were referred to our clinic from September 2012 to June 2015. Twenty-seven [23 females; mean age 43 years old (23–63); mean weight 148 lbs (86–245)] drug-refractory GP patients who underwent surgical implantation of the GES together with the Heineke-Mikulicz PP during the study period were included. There were 17 diabetics (DM) and 10 idiopathics (IP). There was ~71% improvement in TSS in the follow-up evaluation (Table 1). After surgery, the mean retention of the radiolabeled meal decreased by 29.6% and 48.7% at 2 and 4-hrs, respectively and GE was normalized in 60 % of GP patients. There were no post-surgical complications or technical problems related to combining PP with GES.

**Table 1) The severity of upper gastrointestinal symptoms in gastroparetic patients at baseline and after surgery (gastric electrical stimulator implantation plus pyloroplasty).**

|          | Nausea       | Vomiting     | Early Satiety | Bloating    | Post-Prandial Fullness | Epigastric Pain | Epigastric Burning |
|----------|--------------|--------------|---------------|-------------|------------------------|-----------------|--------------------|
| Pre-Op*  | 3.6 (0.4)    | 3.2 (1.2)    | 3.2 (0.7)     | 2.5 (1.3)   | 2.8 (0.9)              | 2.7 (1.4)       | 2.0 (1.8)          |
| Post-Op* | 1.1 (1.1)*** | 0.6 (1.0)*** | 0.9 (1.0)***  | 0.9 (1.2)** | 1.0 (1.1)***           | 1.0 (1.5)***    | 0.9 (1.5) †        |

\* data represents mean (standard deviation), \*\*P<0.01, \*\*\*P<0.001, †n's. not significant

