### Exclusion Criteria:

Organic or pseudo-obstruction, primary eating or swallowing disorders, positive pregnancy test result, psychogenic vomiting, peritoneal dialysis, drug dependent, morbid obesity, active malignancy and whoever received PP or GES in the past.

**D2) Sample Size:** As this study is designed to conclude that pyloroplasty is not inferior to GES plus pyloroplasty, the sample size for the non-inferiority trial by including % normalization of the GE as the binary outcome is calculated based on: "Blackwelder WC."Proving the Null Hypothesis" in Clinical Trials. Control. Clin. Trials 1982; 3:345-353." GE was normalized in 60 % of GP patients with GES-ON

plus Pyloroplasty based on our preliminary data. On the other hand, based on our patients' database, GES alone normalizes GE in around 18% of GP patients, predominantly in idiopathic GP. By defining non-inferiority limit equal to  $(60 - 18 = 42\%)$ , and percentage of success in the GES-ON plus pyloroplasty group, 17 patients will be included in each arm of this study. Therefore, this study is designed to include overall 34 drug-refractory GP patients who will undergo surgery for GES implantation plus pyloroplasty. Based on our records, we have at least 2 surgeries per month; therefore, we predict that it takes approximately 1.5 years to recruit all patients.

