**Histological evaluation of the biopsy samples:** Paraffin embedded formalin fixed tissues will be cut at 3-4 microns thick and mounted on slides containing paired sections from cases and controls. Subsequently, the tissues will be deparaffinized and immunostained by BenchMark XT automated staining instrument. Briefly, the slides will through peroxidase block and antigen retrieval solutions before applying the primary antibodies (C-Kit clone YR145 from Cellmark, Rocklin, CA). Then, the slides will be washed and incubated with the secondary antibody followed by horseradish peroxidase (HPR). At the end, Chromogen will be added and the slides will be counter-stained by Hematoxylin. Pathology slides will be read by a pathologist who will be blind to the diagnosis of the patients, ICC will be counted per high power field (HPF) and the mean of ICC from examining 20 HPF will be calculated. For collagen fibrosis, the biopsies will be stained with trichome. Presence of diffusely distributed collagen between single muscle fibers will be defined as fibrosis and graded as mild, moderate and severe.

**Gastric emptying test:** Gastric emptying test will be performed utilizing a standardized meal consisting of egg beaters labeled with 99m technetium sulfur colloid accompanied by 2 toasts with strawberry jelly and 120 cc of water will be given to the patients (total calories- 240 and 2% fat). Anterior and posterior images will be obtained in the standing position immediately after meal ingestion and at 30 minutes, 1, 2, 3 and 4 hours. Geometric mean calculation and decay correction will be performed on all images. The radiologist will also be blind to the treatment groups.

The radiation exposure of a gastric emptying is equivalent to a chest x-ray or flying across country on an airline. Therefore, this test can be justified for repeating in 3 months.

**D4) Statistical analysis:** In the current study, the following parameters will be analyzed:

- 1) Changes of total gastroparesis symptom scores (TSS) and gastric retention of the radiolabeled meal (%) at 2-4 hrs in each group. TSS will include both severity and frequency.
- 2) Total Symptom Score (TSS) with severity and frequency of gastroparesis symptoms in each etiological subgroup of patients if enough study power would be achieved.
- 3) Associations between changes in gastric emptying and TSS.
- 4) Associations between changes in gastric emptying and ICC count/ pyloric fibrosis.

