- 5) Associations between changes in TSS and ICC count/pyloric fibrosis.
- 6) SF-36, BDI, STAI and PHQ-15 scores and HBA1c (in diabetics) and their association with the treatment as well as gastric emptying/pathological findings.

The normal distribution of the data will be tested based on D'Agostino-Pearson omnibus test, were normality indicates parametric tests. The numerical variables will be reported as means (SD) or Median (Range) at baseline and follow-up visits and will be compared either by appropriate parametric or nan- parametric tests including t-test analysis or Mann–Whitney U test. The time-trends will be analyzed by either Repeated-Measure ANOVA or non-parametric Friedman Test followed by appropriate Post Hoc. Associations will be assessed based on Pearson correlation or Spearman's rho analysis. Data will be presented as bar graphs, time-trend graphs or scatter-plots and tables.

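### Aim 4 is tested by a two-variable correlation with an undefined change score; if a histology marker is related to baseline severity, this can mimic or hide prediction of response

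*Protocol*

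**What the plan says.** The abstract names as a secondary goal the question "whether the baseline pyloric and antral interstitial cells of Cajal (ICC) counts as well as the presence of pyloric fibrosis could predict clinical response to" (the sentence ends with pyloroplasty). Specific Aim 4 asks whether ICC status and/or the presence of "pyloric fibrosis predicts the clinical outcome".

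D4 (Statistical analysis) turns this into two items:
- item 4: "Associations between changes in gastric emptying and ICC count/ pyloric fibrosis"
- item 5: "Associations between changes in TSS and ICC count/pyloric fibrosis"

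The method for both is stated: "Associations will be assessed based on Pearson correlation or Spearman's rho analysis". Each is a two-variable measure. D4 mentions no regression, partial correlation or baseline covariate for these items, and it does not say whether change is absolute or in per cent.

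**The concern.** A change score contains the baseline value. Unless follow-up tracks baseline closely, patients who start worse tend to show the larger fall. A marker that merely accompanies worse entry status will then correlate with change even if it says nothing about response once baseline is known.

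The direction matters. If ICC-depleted patients entered with worse symptoms, they could look like better responders, and a real adverse effect of depletion could be cancelled. Aim 4 is meant to inform who benefits from pyloroplasty, so either error would bear directly on its answer. A later analysis plan could add detail, but the protocol already names the method, and that method leaves baseline out.

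**Working it through.** **Planned size.** The protocol gives no figure for Aim 4. Its 17 per arm (D2) comes from normalization of gastric emptying: 2 × 0.60 × 0.40 × (1.645 + 0.842)² / 0.42² = 16.8, rounded up to 17. The one-sided 5% level and 80% power are inferred, not stated. Aim 4 therefore has at most 34 patients.

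**Step 1: SD of TSS.** Inputs are the Table 1 severity SDs for the six TSS symptoms: before surgery 0.4, 1.2, 0.7, 1.3, 0.9, 1.4; after surgery 1.1, 1.0, 1.0, 1.2, 1.1, 1.5. With a common inter-item correlation r (assumed), SD = √{Σs² + r[(Σs)² − Σs²]}. At r = 0.3:
- baseline: √{6.55 + 0.3 × (34.81 − 6.55)} = √15.03 = 3.88
- follow-up: √{8.11 + 0.3 × (47.61 − 8.11)} = √19.96 = 4.47

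For r from 0 to 0.7 the ranges are about 2.6-5.1 and 2.8-6.0.

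**Step 2: correlation of improvement with baseline.** With baseline and follow-up SDs sB and sP and their correlation ρ (assumed), it is (sB − ρsP) / √(sB² + sP² − 2ρsBsP).

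| ρ | Calculation | Correlation |
|---|---|---|
| 0.3 | (3.88 − 1.34) / √24.58 | 0.51 |
| 0.5 | (3.88 − 2.24) / √17.65 | 0.39 |
| 0.7 | (3.88 − 3.13) / √10.71 | 0.23 |

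The inter-item correlation hardly alters these results. For retention no SDs are given. Over an assumed follow-up/baseline SD ratio of 0.5 to 1 and ρ of 0 to 0.7, the correlation is 0.39-0.89. It comes near zero or turns negative only when the ratio is 1.5-2 and ρ is 0.5 or more.

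**Step 3: what the marker inherits.** Suppose the marker has no effect given baseline and correlates −0.5 with baseline (assumed). Its expected correlation with improvement is −0.5 × 0.51 = −0.26 at ρ = 0.3. At −0.3 it is −0.3 × 0.51 = −0.15.

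**Step 4: false positives for TSS.** Simulation with n = 34, two-sided 5%, the Step 1 SDs at r = 0.3, and ρ from 0.2 to 0.7:

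| Marker-baseline correlation (assumed) | Absolute change | Percent change | Follow-up adjusted for baseline |
|---|---|---|---|
| 0 | about 5% | about 5% | about 5% |
| −0.3 | about 7-14% | 5-12% | about 5% |
| −0.5 | about 11-36% | 5-30% | about 5% |

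A separate run with Spearman's rho on absolute change, restricted to ρ of 0.2-0.5, gave 10-15% and 18-33%.

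**Step 5: masking.** Take equal SDs, ρ = 0.3, a marker-baseline correlation of −0.5, and a true effect of −0.4 baseline SD of follow-up per SD of marker (all assumed). The plain correlation with change averages about 0.05, with 6% power. Adjusted for baseline it is about 0.34, with 52% power.

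**The case against.** Several counter-arguments carry weight.

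- **The form of change is not fixed.** A reader might infer that the protocol specifies raw change. It does not, and its pilot results are in per cent ("the mean retention of the radiolabeled meal decreased by 29.6% and 48.7% at 2 and 4-hrs"). If every patient improved by the same proportion, percent change would hold its false-positive rate (5.1-5.6% in simulation). But Table 1 does not fit that model: a uniform 69% fall would shrink the nausea SD from 0.4 to about 0.12, and it rises to 1.1. With the Table 1 SDs, percent change reaches 30% false positives.
- **The marker-baseline link is assumed.** A reader might infer that depleted patients do start worse. The background section gives only how common depletion is (about 40% antral, more than 70% pyloric) and nothing on its relation to retention or symptoms.
- **Table 1 means are not patient-level evidence.** The symptoms that start highest fall most (correlation 0.96 across the seven symptom means), but this compares symptoms, not patients.
- **Etiology is only an indirect path.** The statement that "GES alone normalizes GE in around 18% of GP patients, predominantly in idiopathic GP" and the 58% versus 48% symptom response in C2 concern stimulation without pyloroplasty. Nothing says that ICC count or fibrosis differs by etiology. Etiology is worth including because allocation is organized by it, not because confounding has been shown.
- **Adjustment is not always unbiased.** The marker is observed, not randomized. If every patient fell by a constant amount and baseline were measured with error, the change-score correlation would hold 5%, while the adjusted model would give about 7-22% false positives in simulation. A constant fall is hard to credit here, because patients are selected for high values and scores fall by about 70% towards a floor of zero. The point still justifies keeping the change-score analysis as a supplement.

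**Conclusion.** The point holds in conditional form. The protocol ties Aim 4 to a two-variable correlation with an undefined change score, and that score is likely to depend on baseline. The dependence is moderate for TSS (roughly 0.2-0.5, from the pilot SDs with ρ assumed at 0.3-0.7). For retention it rests on assumed SDs alone.

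Whether this distorts the answer depends on how the markers relate to baseline severity, which the trial can measure but the protocol does not report. The documents do not support a claim that Aim 4 will give a false or reversed result; they support only that the planned analysis could not tell such a result from a true one. Because the aim is secondary and 17 per arm rests on normalization of gastric emptying, the importance is minor to moderate.

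**What to change.** In D4, replace items 4 and 5 as the main Aim 4 analysis by a regression of the 3-month value (retention in one model, TSS in another) on the ICC count or fibrosis grade. Include the patient's own baseline value, treatment arm and etiology as covariates. Arm belongs in the model because the background section frames prediction over both the ON and OFF periods. Report the adjusted association with its confidence interval, and show the marker-baseline correlation beside it so that readers can judge how much adjustment mattered.

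Keep the change-score correlation as a supplementary analysis, and state whether change is absolute or in per cent. If the two analyses disagree, report both and say so.

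Cost: wording only, since baseline retention, TSS and etiology are already collected. The three covariates use three degrees of freedom, taking the residual from 32 to 29 with 34 patients. The number may be lower, because tissue requires consent under a separate protocol. The sample size does not change.

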**D3) Study Design:** After receiving IRB approval, the patients will be screened and the project will be discussed with the potential candidates for GES implantation plus pyloroplasty. Based on the inclusion/exclusion criteria, the baseline gastric emptying test (GET) based on the 4-h standardized radionuclide solid meal protocol will be performed and 34 patients will be included in the study. Our effort would be to include similar numbers of idiopathic and diabetic patients in each intervention group based on a block randomization method. The patients will be followed up for 1 month, while their PAGI-SYM, PAGI-QOL and TSS severity/frequency will be recorded on a Standardized Symptoms Interview Form, which assesses the symptoms of gastroparesis occurring during the last 2 weeks before the interview for severity of vomiting, nausea, early satiety, bloating, postprandial fullness, and epigastric pain. The severity of each symptom will be graded by the patients as 0=absent, 1=mild (not influencing usual activities), 2=moderate (diverting from, but not urging modifications, of usual activities), 3=severe (influencing usual activities, severely enough to urge modifications), and 4=extremely severe (requiring bedrest). The sum of the severity ratings of the six symptom subscores comprises the overall total symptom score (TSS) in severity.

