PAGI-SYM and TSS questionnaires will be filled every 2 weeks during the study period. GES implantation together with the Heineke-Mikulicz PP will be performed laparoscopically (<10% of cases may require open approach). Only one surgeon using the same technique at all times will perform the surgeries. In GES-ON group, GES will be turned on immediately after the operation. On the other hand, in GES-OFF group, the GES will remain OFF for the first 3 months, while symptoms will be recorded again in both groups. After 3 months, follow up GET will be performed and in GES-OFF group, the device will be turned ON. Both groups will be followed for 3 more months clinically, to record any possible changes in their symptoms. Moreover, 36-Item Short Form Health Survey (SF-36), Beck depression inventory (BDI), State-trait anxiety inventory (STAI) and the patient health questionnaire (PHQ-15) will be completed at baseline followed by 3 and 6 months after the surgery. The amount of anti-emetics and prokinetics, days of hospitalization and ED visits and any possible complication will be recorded during the study period. Glucose control in diabetic patients will be monitored by HbA1c. Pain will also be monitored regarding narcotic need. During the follow-up patients will be instructed to remain on a mechanical soft diet of smaller meals, low fat, and low fiber. Evaluators of clinical outcome, the radiologist and the biostatistics consultant as well as the patient will remain blind to the GES-ON or -OFF status before the results get finalized. The individual programming the device will have no clinical rule to avoid any bias.

One of our Investigators, [name] is assigned to serve as an un-blind person, who is going to generate a master list of participants by dividing them into two groups based on their etiologies (diabetic or idiopathic). All efforts would be to include similar numbers of idiopathic and diabetic patients in each intervention group based on a block randomization method, allowing for GES to be turned ON at the surgery, or it will stay OFF for the 3-month-long blind portion of the study.

The following flow-diagram summarizes the steps of this study:

[figure not shown]

Early termination of the study will occur if a patient decides not to continue the study or if in the GES-OFF group, the nausea/vomiting symptoms are not manageable after 6 weeks of the operation, which is the usual time for surgical healing.

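### D4 does not tie the 2-weekly TSS forms of the blinded phase to the ON-versus-OFF comparison, so that comparison is less precise than the planned data allow

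*Protocol*

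**What the plan says.** **Collection (D3).** "PAGI-SYM and TSS questionnaires will be filled every 2 weeks during the study period". The TSS form is one "which assesses the symptoms of gastroparesis occurring during the last 2 weeks before the interview", so forms filled on schedule do not overlap. Before describing the surgery, D3 states: "The patients will be followed up for 1 month, while their PAGI-SYM, PAGI-QOL and TSS severity/frequency will be recorded".

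**Randomised contrast (D3).** "in GES-OFF group, the GES will remain OFF for the first 3 months, while symptoms will be recorded again in both groups". The OFF devices are then turned on and both groups are followed for 3 more months, so the arms differ by design only in the first 3 months. D3 allows the blinded phase to end early in the OFF group if nausea and vomiting are unmanageable after 6 weeks. Amendment 2, item 8, clarifies that such patients remain in the trial.

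**Analysis (D4).** The first item is "Changes of total gastroparesis symptom scores (TSS) and gastric retention of the radiolabeled meal (%) at 2-4 hrs in each group". On tests: "The numerical variables will be reported as means (SD) or Median (Range) at baseline and follow-up visits and will be compared" by parametric or non-parametric methods, "including t-test analysis or Mann–Whitney U test". The next sentence assigns time-trends to repeated-measures ANOVA or the Friedman test, with post hoc tests.

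**Visit timing (Amendment 2, item 3).** The 3- and 6-month follow-ups have a grace period of 6 weeks on either side.

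**The concern.** Aims 1 and 3 need a symptom comparison between stimulation ON and OFF after pyloroplasty. The only tests in D4 that directly compare two independent groups are attached to values at visits. Read as written, one 2-week report at baseline and one at follow-up can carry the contrast, although about six forms per patient fall in the blinded phase.

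The time-trend sentence does not clearly fill the gap. The Friedman test examines time within one group and cannot compare arms. Repeated-measures ANOVA could compare them, but D4 names no group term and no time window.

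At stake is the width of the TSS interval in a trial of 34 patients that was not sized on TSS. The visit window adds a second problem: the 3-month value may come from quite different times after surgery in different patients.

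**Working it through.** **1. The plan's own figure.** D2 gives 17 per arm from a 60% normalisation rate and a margin of 60 − 18 = 42 points. It states neither alpha nor power. With one-sided 0.05 and 80% power (assumed):

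n = (1.645 + 0.842)² × 2 × 0.6 × 0.4 / 0.42² = 6.18 × 0.48 / 0.1764 = 16.8, i.e. 17.

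The figure reproduces, but it concerns gastric emptying. The protocol gives no precision or power figure for TSS.

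**2. Forms available.** Three months is about 13 weeks, so about 6 forms after surgery carry the ON-versus-OFF contrast. One month gives up to 2 forms before surgery, if that month is pre-operative and the 2-weekly schedule covers it (assumption).

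**3. Visit window.** 13 − 6 = 7 and 13 + 6 = 19, so a 3-month visit value may come from about week 7 to week 19.

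**4. Variance of the arm contrast.** Assume equal variances (set to 1), correlation rw between forms in the same phase and rb between a pre- and a post-operative form. The documents give neither, so I take rw = 0.6–0.8 and rb = 0.2–0.5.

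- One form at each end: change score 2 − 2rb; baseline-adjusted (ANCOVA) 1 − rb².
- Mean of 3 blinded and 2 baseline forms: vf = (1 + 2rw)/3 and vb = (1 + rw)/2. Change score vf + vb − 2rb; ANCOVA vf − rb²/vb.

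Example, rw = 0.7 and rb = 0.4: vf = 0.80, vb = 0.85. Change: (0.80 + 0.85 − 0.80)/1.20 = 0.71. ANCOVA: (0.80 − 0.16/0.85)/0.84 = 0.73.

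| rw | rb | Ratio, change | Ratio, ANCOVA |
|---|---|---|---|
| 0.6 | 0.2 | 0.71 | 0.71 |
| 0.6 | 0.5 | 0.53 | 0.56 |
| 0.7 | 0.2 | 0.78 | 0.78 |
| 0.7 | 0.4 | 0.71 | 0.73 |
| 0.7 | 0.5 | 0.65 | 0.67 |
| 0.8 | 0.2 | 0.85 | 0.86 |
| 0.8 | 0.5 | 0.77 | 0.79 |

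Each ratio compares like with like. Any gain from replacing change scores by ANCOVA is not counted.

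**5. On the standard-error scale.** √0.53 = 0.73 and √0.86 = 0.93, so the standard error is 27% to 7% smaller; at 0.70, √0.70 = 0.84, or 16% smaller. In patients per arm: 17/0.86 = 20, 17/0.70 = 24, 17/0.53 = 32.

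**6. Sensitivity at rw = 0.7, rb = 0.4.**

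- Only one baseline form exists: change (0.80 + 1 − 0.80)/1.20 = 0.83; ANCOVA (0.80 − 0.16)/0.84 = 0.76.
- All six blinded forms and two baseline forms: vf = (1 + 5 × 0.7)/6 = 0.75; change (0.75 + 0.85 − 0.80)/1.20 = 0.67; ANCOVA (0.75 − 0.188)/0.84 = 0.67.

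Going from three to six blinded forms adds little, so the choice of weeks can rest on clinical relevance.

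**The case against.** **D4 does not limit TSS to two forms.** It speaks of visits in the plural, its list of tests is not exhaustive, and it plans a longitudinal analysis. A reader might infer that the 2-weekly forms are thrown away. The text does not support that: the time-trend analysis may well use them. What stands is that no sentence commits them to the comparison of arms.

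**Which forms to use is a matter for a statistical analysis plan.** One may exist and settle it. But D4 does not simply defer. It names a visit-based comparison and an unbounded time-trend test, and a more precise comparison is available from the same data.

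**Dilution by the second 3 months.** A reader might infer that the time-trend analysis halves a stimulation effect, because about 6 ON-versus-OFF forms are averaged with about 6 ON-versus-ON forms: (6δ + 0)/12 = δ/2. That holds only for a group effect pooled over 6 months, with a constant effect and no carry-over. D4 specifies no such effect, and a group-by-time analysis would avoid it.

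**Direction.** A reader might infer that an imprecise comparison favours the conclusion the trial seeks. Under the non-inferiority aim in D2, a wider interval makes the claim harder to reach. It would help only if a non-significant test were read as equivalence.

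**Restricting to late weeks.** D3 mentions 6 weeks after the operation, "which is the usual time for surgical healing", only to time early termination. It does not call earlier forms uninformative. Stimulation in the ON arm starts immediately after surgery, so weeks 2–6 are randomised data too. A fixed late window could also pick up forms completed after an early end of the blinded phase. The fix must handle both.

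**Conclusion.** The point holds as a loss of precision and an unfixed choice of forms. D4's named between-arm tests rest on visit values that may lie anywhere from about week 7 to week 19, and its time-trend analysis has no stated group term or limit to the blinded 3 months.

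Under the assumed correlations, three blinded and two baseline forms instead of one of each leave 0.53–0.86 of the variance. The standard error is about 7–27% smaller, centrally about 16%. The size rests on those correlations, equal variances, two usable baseline forms and three usable blinded forms, with a similar effect across the weeks chosen. A single headline figure of 30% would be a variance figure at one assumed setting, not a quantity from the protocol.

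This is worth correcting because it costs almost nothing and the trial is small. It does not make the planned comparison invalid.

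**What to change.** Amend D4 as follows:

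- Make the randomised TSS comparison a between-arm contrast of the 2-weekly forms from the blinded phase only: either their mean per patient, or a repeated-measures model with a group term.
- Use the mean of the pre-operative forms as baseline covariate.
- Prespecify which blinded-phase weeks count, and say whether the early post-operative weeks are among them.
- Keep forms completed after an OFF device is switched on out of this contrast, judged by the actual switch-on date, and report them descriptively.
- Let patients whose blinded phase ends early contribute their forms up to that point rather than be dropped. If the chosen weeks start late, say how a patient with no form in them is handled.

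The cost is a paragraph in D4, with no new visits, forms or patients. The small downside is that the result describes an average over the chosen blinded weeks rather than the 3-month value alone. The 3-month visit value can still be reported beside it.

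### D4 leaves out the outcome and the limit on which D2 sizes the trial, so the stated analysis cannot support the non-inferiority conclusion

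*Protocol*

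**What the plan says.** D2 (Sample Size) states the objective: "this study is designed to conclude that pyloroplasty is not inferior to GES plus pyloroplasty". It sizes the trial "by including % normalization of the GE as the binary outcome", citing a published non-inferiority method. The reference rate is that "GE was normalized in 60 % of GP patients with GES-ON" plus pyloroplasty, and the comparator used to build the limit is that "GES alone normalizes GE in around 18% of GP patients". The limit is 60 − 18 = 42 percentage points, and the result is 17 patients per arm, 34 in all.

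D3 (Study Design) provides a follow-up gastric emptying test at 3 months, at the end of the blinded ON/OFF phase.

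D4 (Statistical analysis) lists six sets of parameters. Gastric emptying enters the first as a continuous measure: "Changes of total gastroparesis symptom scores (TSS) and gastric retention of the radiolabeled meal (%) at 2-4 hrs in each group". The others are symptom scores by etiology, associations with symptoms and with pathology, and questionnaire scores with HbA1c. On methods, D4 says that numerical variables "will be compared either by appropriate parametric or nan- parametric tests including t-test analysis" or the Mann–Whitney test. Time trends get repeated-measures ANOVA or Friedman, and associations get Pearson or Spearman correlation.

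Neither amendment changes the analysis of gastric emptying.

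**The concern.** The two sections describe different trials. D2 describes a non-inferiority comparison of two proportions against a fixed limit. D4 describes tests whose null hypothesis is no difference, applied to continuous variables. The outcome that determined the sample size is not analysed, and the limit is not used after D2.

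What is at stake is the trial's main conclusion. A non-inferiority claim needs the confidence limit for the difference to exclude the margin. A difference test cannot supply that: with few patients it can be non-significant because the data are sparse, whatever the true deficit. Since D4 offers no other analysis bearing on the D2 objective, a non-significant p-value could be taken as the answer.

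**Working it through.** **1. Does the sample size reproduce?** Inputs from D2: 60% in both arms under the design assumption, margin 0.42. Alpha and power are not stated, so they are assumed. For two proportions with unpooled variance:

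n per arm = (z₁₋α + z₁₋β)² × [p₁(1 − p₁) + p₂(1 − p₂)] / margin²

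With one-sided alpha 0.05 and 80% power: (1.645 + 0.842)² × (0.24 + 0.24) / 0.42² = 6.18 × 0.48 / 0.1764 = 16.8, so 17. This matches D2. Over one-sided alpha 0.005 to 0.10 and power 80% to 95%, it was the only combination tried that gives exactly 17. One-sided 0.10 comes close (15 at 85% power, 18 at 90%). One-sided 0.025 gives 22 at 80% power.

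**2. What does 17 per arm give for a margin test?** SE = √(0.48/17) = 0.168 and 0.42/0.168 = 2.50. Power is Φ(2.50 − 1.645) = 80% at one-sided 0.05, and Φ(2.50 − 1.960) = 70.5% at one-sided 0.025. Exact enumeration with a Wald limit gives 81% and 71%.

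**3. D2 against D4.**

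| | D2 | D4 |
|---|---|---|
| Aim | non-inferiority | differences, trends, associations |
| Emptying variable | proportion normalised | % retention and its change |
| Reference value | limit of 42 points | none stated |
| Method | non-inferiority for a binary outcome | t-test or Mann–Whitney; ANOVA or Friedman; correlations |

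**4. How far apart can the two approaches be?** D4 names no test for proportions, so Fisher and uncorrected chi-square (two-sided 0.05) stand in as illustrations. The true rates are ON 60% and OFF 18%, a deficit of 42 points, exactly at the limit. All outcomes of two Binomial(17) arms were enumerated:

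- Difference test non-significant: 25% (chi-square), 38% (Fisher).
- Wald lower limit above −42 points: 4.1% at one-sided 0.05, 1.9% at one-sided 0.025.

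Reading non-significance as non-inferiority would therefore carry a false-claim rate at the limit about six (25.3/4.1) to nine (38.5/4.1) times that of the margin test at one-sided 0.05.

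**5. One possible data set.** ON 10/17, OFF 5/17. Fisher p = 0.17 and chi-square p = 0.084, both non-significant. The difference is −29 points, with SE = √[(0.588 × 0.412 + 0.294 × 0.706)/17] = 0.163. The one-sided 95% lower limit is −0.294 − 1.645 × 0.163 = −0.56. That lies below −0.42, so non-inferiority is not shown.

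**The case against.** The strongest reply is that D4 is incomplete rather than wrong. The sentence on group comparisons covers numerical variables and is open-ended; it does not say that the binary outcome will be t-tested. D2 already fixes the aim, outcome, limit and method source, and a statistical analysis plan that is not at hand may hold the rest. Part of this stands: the interval method, stratification and similar detail can properly be left to such a plan. But the protocol does not defer its analysis. It sets out what will be analysed, and that list omits the outcome and limit on which the trial was sized.

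A reader might also infer more than the document supports:

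- *That non-significance will be read as non-inferiority.* No section says so. It is a risk created by the gap, not a stated rule.
- *That the plan is biased toward the sponsor's hypothesis.* D2 speaks of a design to conclude non-inferiority, but the abstract and background ask openly whether pyloroplasty alone is enough.
- *That non-significance at milder deficits is a false conclusion.* With OFF at 40% or 30%, Fisher is non-significant 86% or 69% of the time (chi-square 77% or 55%). Those deficits, 20 and 30 points, lie inside D2's own limit, so pyloroplasty alone counts as non-inferior there. Whether 42 points is a suitable limit is a separate question.
- *That a missed difference is the likely result at the limit.* It is not: both tests detect it more often than not (62% and 75%).
- *That the same can be quantified for the symptom score.* D2 sets no margin for it, and the protocol gives no SD for its change, so such a figure would say nothing about the claim that was sized.

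**Conclusion.** The point holds as an internal mismatch between D2 and D4, and it should be fixed before analysis. It rests on the text alone: D4 does not analyse the normalisation proportion, uses no limit, and its between-group tests are tests of no difference on numerical variables.

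The figures, 25% to 38% against about 4%, illustrate the consequence at the D2 limit. They assume 17 evaluable patients per arm, a true ON rate of 60%, Fisher or chi-square as the difference test, and a Wald limit at one-sided 0.05. They show what would follow if a non-significant test were taken as non-inferiority, which the protocol does not say will happen.

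**What to change.** Add to D4, ahead of the present list, one confirmatory analysis: the GES-OFF minus GES-ON difference in the proportion with normalised gastric emptying at the 3-month test, with a lower confidence limit compared with the prespecified D2 margin. Non-inferiority is claimed only if that limit lies above the negative of the margin.

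Three statements should go with it:

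- **Definition of normalisation.** The protocol gives none. One option is meeting neither entry threshold, that is, retention of 60% or less at 2 h and 10% or less at 4 h.
- **One-sided alpha.** At 0.05, 17 per arm keeps about 80% power. At 0.025 power falls to about 70%, and 22 per arm would be needed for 80%.
- **Interpretation.** A non-significant t-test, Mann–Whitney or other difference test is not evidence of non-inferiority.

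Stratification by etiology and a Miettinen–Nurminen interval are reasonable options, not corrections of an error. The existing D4 analyses can stay as secondary.

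The cost is a few sentences and little analysis work. The 3-month test is already collected, and the sample size need not change if one-sided 0.05 with 80% power was intended.
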